**7.7 Other Evaluations**

- Complete physical examination, including height and weight
- Vital signs (oral Temperature, pulse, glood pressure) pre- and post-dose;
- Complete inventory of concomitant diseases and medical history;
- Complete inventory of concomitant medications for non-MS conditions in 30 days prior to screening;
- Complete MS history, including:
  - Onset first symptom and date of diagnosis;
  - Number of relapses in the last year prior to study entry;
  - Inventory of concomitant medications for MS symptomatic treatment during one year prior to study entry;
  - Previous MS treatment at any time;
  - Assure documentation of the most recent relapse (records must be maintained in the source documents, as described in section 14.3);
    - Complete neurological examination, including: Functional Systems Status Evaluation
    - Ambulation Index
    - Kurtzke EDSS
    - 10 Meter Walking Test , 9-Hole-peg test PASAT cognition test.
  - ECG.

Side effects will be closely monitored for 7 days after each injection of the vaccine and thereafter during the regular follow-up visits (time points).

Each enrolled patient should inform the treating physician about every symptom occurring within the 7-day period after injection. Physicians in charge will be available of phone calls contact for all period of the study.

Signs and symptoms will be recorded and scored/graded according to the WHO classification.

### Local signs

Site of subcutaneous injection: -> pain: 0=absent; 1=mild (slight discomfort); 2=moderate (resolved by common analgesic therapy); 3=severe (not resolved by analgesic drug, confined to home).

### Systemic symptoms

Fever: 0=absent; 1=mild (less than 38oC); 2=moderate (38-39oC); 3=severe (over 39oC).

Headache: 0=absent; 1=mild (slight discomfort); 2=moderated (resolved by common antalgic therapy); 3=severe (not resolved by common antalgic drugs).

Asthenia: 0=absent; 1=mild (not interfering with normal life); 2=moderate (interfering with normal life but not requiring bed resting); 3=severe.

**8. CONCOMITANT MEDICATIONS**

**8.1 Allowed Concomitant Medications**

**8.1.1 Symptomatic MS Medications**

Symptomatic MS agents, such as anti-cholinergic and spasmolytic drugs are permitted at clinically appropriate doses.

**8.1.2 Cortico-steroid Therapy During Exacerbation**

Short-term (3-7 days) treatment with cortico-steroids will be allowed during acute relapses. The recommended protocol treatment is a fixed dose of I.V. Solumedrol (Methyl-Prednisolon) 1gr/day.

No tapering off is allowed. **Oral steroids are not allowed.**

**8.1.3 Other Allowed Medications**

Other medications not listed in Paragraph 8.2 (below) may be given concomitantly as needed for the patient’s welfare. Administration of al medications, including indication, dose, time, and route of administration, will be recorded in the Case Report Form.

**8.2 Prohibited Medications**

- Interferons;
- Parenteral steroids treatment;
- Oral steroids;
- Chemotherapeutic therapy;
- Immunosuppressive or immuno-modulating drugs;
- IVIg and any other experimental drugs.

**9. STUDY CONDUCT**

The study assessments will be performed according to the study task flow chart.

**9.1 Pre-Enrollment (Screening) Evaluation (Visit 1)**

The patient will be assessed for eligibility criteria by the Treating Physician and neurologically examined by the Examining Physician. Patient’s pre-enrollment must occur within 60 days prior to randomization and the first treatment. Screening evaluation must assure that all inclusion and exclusion criteria have been met.

During the screening visit, the patient must be thoroughly informed about all aspects of the study, including scheduled study visits and activities, and must sign the informed consent.

The following procedures will then be performed:

- Physical examination;
- Vital signs;
- Medical history;
- Historical/concomitant medications;
- History of multiple sclerosis;’
- Neurological evaluation;
- ECG and Chest X-rays;
- Clinical laboratory studies, including:
  - Serum pregnancy test (β HCG) for women;
  - Urinalyses;
  - Hematology;
  - Serum chemistry;
  - Serum samples and lymphocytes for immunological studies.

- Evidence of relapse;

- Inclusion/exclusion criteria;

- - 1. **Screening for patients that their T-cells react to the specific peptide**

Cell preparation and cell proliferation**:** 50 ml of peripheral blood will be drawn from MS patients, supplemented with 10 IU/ml heparin. Peripheral blood mononuclear cells (PBMC) will be isolated by Ficoll Paque (Pharmacia Biotech, Uppsala, Sweden) density centrifugation. Cells will be washed with RPMI with autologous serum. The culture medium contains RPMI supplemented with 1% sodium pyruvate, 1% l-glutamine (200 mM each), gentamicin (20µg/ml) and 2% Hepes (1 M, pH 7.3) (Biological Industries, Kibbutz Beit Haemek, Israel). PBMC will be plated in 96 well round-bottomed micro plates (Falcon, Lincoln Park, NJ., USA) at a cell concentration of 2x105 cells/ well. Each well will contain 100 µl of 2x106 cells/ml and 100µl of medium with twice the recommended antigen concentration. The above assay will be performed in replicates of five. Five wells with cells and medium without antigen will be incubated as a background control. The antigens that will be used in the proliferation assay and their final concentrations are: PHA (Murex Diagnostic Ltd. England) 0.3 µg/ml; tetanus toxoid (Connaught Lab. Inc. Pen. USA) 5 µg/ml; *Candida albicans* (Miles, WA. USA) 20 µg/ml; PPD (Statens Institute, Denmark); synthetic peptides of the human PLP 41-58, 184-199, 190-209, MBP 83-99, 87-110 and 151-170 and MOG 6-26, and 34-56 (obtained from Chiron, produced in a GLP facility that has been approved by the US Institutional Review Boards for use in clinical study identical to this protocol), 5-20 µg/ml. The plates will be incubated at 37oC in a 5% CO2 humidified incubator. After seven days, cell proliferation will be assayed by 3H-thymidine incorporation to DNA determined using scintillation liquid in λ-particle counting (Packard model 2000 counter reader). Radioactive counts per minute (cpm) will be compared between cells cultured with or without the antigens. The proliferation values will be represented as a stimulation index value (S.I.), *i.e*. cpm with antigens divided by the cpm without the antigen (cpm below 300 will not be considered). S.I. values greater than or equal to 2 will be considered to be positive. Positive patients to PLP, MBP and/or MOG will be considered as fulfilling one of the inclusion criteria's.

**9.2 Preparation of TCV (Visits 2-7)**

Patients will visit the clinic weekly for blood withdrawals. Antigen presenting cells (APC's) will be extract from their blood to facilitate the proliferation of specific T-cell lines.

**9.3 Month 0 Baseline Evaluation – First Day of Treatment (Visit 8)**

Prior to randomization, the following will be assessed:

- Changes in medical condition since screening;
- Concomitant medication changed since screening;
- Physical changes since screening;
- Clinical laboratory tests; Routine hematology, blood chemistry, and urinalyses
- Neurological exams including FS, AI, EDSS, 10 Meter Walking Test, 9-Hole-peg test PASAT cognition test.
- Evidence of relapse;
- MRI
- Inclusion/Exclusion criteria confirmation;
- Pre-dose vital signs.

**9.3.1 Randomization**

Randomization will be determined according to a computer-generated randomization list. On the day of the TCV initiation, each patient will be allocated a number in sequential chronological order. The patient will then be assigned a medication according to his/her sequential number. Prior to allocation of patient number, all patients should be identified by their initials, date of birth, and screening number.

The randomization code for each patient will be delivered to the PI (see section15.1.1: treating physician) in individual sealed envelopes for emergency use only. Only in case of a serious adverse event, when the information contained in the envelope is urgently needed for the treatment of the patent, should the investigator open the relevant sealed emergency envelope containing that patient’s treatment allocation. If possible, the CRO should be notified of the event prior to breaking of the code.

On completion of the study, the emergency code envelopes will be collected by the CRO or by the CRO’s authorized representative.

**9.3.2 Post Randomization Procedures**

T-cell vaccination or placebo will be administrated to patients (first treatment at visit 8). The empty tubes will be disposed to biohazard waste without disclosing the labels.

**9.4 Treatment Period (visits 8-11).**

The treatment period will include 4 visits (Visits 8-11), on day 1 (first injection) and months 1, 3, and 6. Following the first injection of the TCV (visit 8) there will be additional 3 boosts of the TCV that will be schedule to month 1, 3, 6 (visits 9, 10, 11). Two subcutaneous (S.C.) injections (1.5-3 ml of dead cell preparation) will be prepared each time: one for each arm and each will contain a mixture of lines specific for one protein. For the schedule of injections and visits, see the following table:

| **Visit** | **Injection #** | **Day #** | **# of Fixed Cells** |
| --- | --- | --- | --- |
| **8** | **1** | **1** | **10-50 x 106** |
| **9** | **2** | **30** | **10-50 x 106** |
| **10** | **3** | **90** | **10-50 x 106** |
| **11** | **4** | **180** | **10-50 x 106** |

In addition the patients will be examined.

- Neurological assessment will be performed at months 1, 3, and 6. The Examining Physician **should not** refer to previous neurological assessments carried out on the patient, prior to the completion of the visit’s neurological assessment;
- Routine hematology, blood chemistry, ad urinalyses will be performed at months 6 (visit 11).
- Documentation and follow-up of each exacerbation will be conducted through the study period.
- Adverse events will be followed carefully at each visit by the Treating Neurologist;

The injection site on the patients arm will be covered by bandage before the examination. Thus, the evolution will not be biased by differences between the placebo and the TCV at injection site.

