| **Primary Outcome Measures** | The primary efficacy end-point for this study is The ∆ EDSS that will be calculated for each patient by subtracting the beginning and end point EDSS scores. Mean EDSS scores for the two groups (treatment vs. placebo) will be calculated.  The primary safety endpoint for this study are the safety profile of adverse experiences, the tolerability will be based on the number of patients completing the study  The total number of relapses observed during the monitored period. |
| **Secondary Outcome Measures** | Changes from the baseline of clinical parameter; 10 meter walking test, 9-Hole-peg Test, PASAT cognition test and the Ambulatory Index (AI).  The total number of T1-Gd enhancing lesions (in MRI) and of T1 hypo dance black holes.  The volume of T2 lesions: (in MRI) and the degree of brain atrophy i.e. BPF (brain parenchymal factor) width corpus colossus and of lateral ventrical).  Safety profile of clinical laboratory parameters, the vital signs and ECG |
| **Tertiary Outcome Measures** | Proportion of relapse free patients  Time to first relapse.  Proportion of second relapse free patients  Time to second relapse.  Brain atrophy (whole brain).  Number and proportion of activated lymphocytes.  Number and proportion of anti-myelin reactive lymphocytes in the peripheral blood and IgG antibody levels in the cerebrospinal fluid |
| **Statistical Consideration** | Randomization: a total of 30 patients will be randomized into two treatment arms (1:2). 10 patients for the placebo and 20 patients for the vaccination. |

1. **ABBREVIATIONS**

CRF Case report Form

CRO Contract Research Organization

EAE Experimental Allergic Encephalomyelitis

EC Ethics Committee

EDSS Expended Disability Status Scale

FDA Food and Drug Administration

GMP Good Manufactory Practice

IRB Institutional Review Board

MBP Myelin Basic Protein

MOG Myelin Oligodendrocyte Glycoprotein

PLP Proteolipid Protein Peptides

QA Quality Assurance

QC Quality Control

R-P MS Relapsing-Progressive MS

R-R MS Relapsing-Remitting MS

SAE Serious Adverse Event

S.C. Subcutaneous

SOP Standard Operating Procedure

T1 Relaxation Time T1

T2 Relaxation Time T2

TCV T-Cell Vaccination

1. **INTRODUCTION**

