**Study Activities Flow Chart**

**STUDY TASK FLOW SHEET**

| Procedures | Screening | TCV Processing | Baseline | On Study Evaluation | | | | | |
| --- | --- | --- | --- | --- | --- | --- | --- | --- | --- |
|  | | | TC Injections | | | |  | | |
| *Visits* | 1 | 2-7* | 8 | 9 | 10 | 11 | 12 | 13 | 14 |
| *Months* | *-3* | -2 | 0 | 1 | 3 | 6 | 8 | 10 | 12 |
| Informed Consent | X |  |  |  |  |  |  |  |  |
| Eligibility Criteria | X |  |  |  |  |  |  |  |  |
| Medical History | X |  |  |  |  |  |  |  |  |
| Historical and  Concomitant Medications | X |  | X | X | X | X | X | X | X |
| Physical Examination | X |  |  |  |  |  |  |  | X |
| Neurological Exam and test | X |  | X | X | X | X | X | X | X |
| Laboratory Evaluation/Immunology |  |  | X |  |  | X |  |  | X |
| Serum β HCG | X |  |  |  |  |  |  |  | X |
| MRI-cerebral |  |  | X |  |  |  |  |  | X |
| Randomization |  |  | X |  |  |  |  |  |  |
| TCV |  |  | X | X | X | X |  |  |  |
| Adverse Experiences |  |  | X | X | X | X | X | X | X |

* Weekly visits for blood withdrawals for TCV preparation.

Preparation of T-cell Vaccination

Activity Flow Chart

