**9.5 Follow up period (visits 12, 13)**

The follow up period will be (Visits 12-13), on months 8, and 10. The TCV treatment protocol will be performed as follows:

- Neurological assessment will be performed at months 8, and 10,. The Examining Physician **should not** refer to previous neurological assessments carried out on the patient, prior to the completion of the visit’s neurological assessment;
- Documentation and follow-up of each exacerbation will be conducted through the study period.
- Adverse events will be followed carefully at each visit by the Treating Neurologist.

The injection site on the patients arm will be covered by bandage before the examination. Thus, the evolution will not be biased by differences between the placebo and the TCV at injection site.

- 1. **Termination (visit 14)**

The termination visit will include the following procedures:

- Physical examination;

- Vital signs;

- Clinical laboratory evaluation, routine hematology, blood chemistry, and urinalyses will be performed;

- Adverse experiences;

- Concomitant medication;

- Complete neurological examination including FS, AI, EDSS, 10 Meter Walking Test, 9-Hole-peg test, PASAT cognition test.

- Evaluation of relapse;

- MRI

- Termination of double blind phase procedures;

- If an AE is present at the last follow-up visit, it will be followed until the medical condition returns to baseline or is considered stable or chronic

The injection site on the patients arm will be covered by bandage before the examination. Thus, the evolution will not be biased by differences between the placebo and the TCV at injection site.

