**9.7.2.1 Study Premature Discontinuation Criteria**

- Patient with any clinical intolerable adverse experience/event; **(of grade III or IV) according** to the WHO classification and, in particular, in case of a severe manifestation of hypersensitivity consecutive to a vaccine injection, or of a severe alteration of renal and/or hepatic functions (creatinine clearance lower than 70 ml/min. and ASAT and/or ALAT transaminases higher than 6 times the normal value.
- Patient’s decision to discontinue treatment.
- Initiation of treatment with any other investigational agent;
- Pregnancy’
- Lost to follow-up;
- PI’s decision to prematurely terminate the study for safety or any other reasons.

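### ECG is a secondary safety endpoint with no scheduled post-dose recording, and no laboratory test is scheduled between the first and fourth injection visits although laboratory discontinuation limits are set

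*Protocol*

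**What the plan says.** **ECG.** The synopsis (Secondary Outcome Measures) includes "Safety profile of clinical laboratory parameters, the vital signs and ECG", and the list of secondary safety endpoints in section 4 repeats ECG. The screening visit in section 9.1 lists "ECG and Chest X-rays". Section 7.7 names ECG among the other evaluations but gives no time for it.

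**Laboratory limits.** Section 9.7.2.1 gives, as part of the criteria for premature discontinuation, "creatinine clearance lower than 70 ml/min. and ASAT and/or ALAT transaminases higher than 6 times the normal value".

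**Laboratory schedule.** Section 9.1 lists chemistry, hematology and urinalysis at screening. At visit 8, before randomization, section 9.3 lists "Clinical laboratory tests; Routine hematology, blood chemistry, and urinalyses". For the treatment period, section 9.4 says "Routine hematology, blood chemistry, ad urinalyses will be performed at months 6 (visit 11"). At the termination visit (visit 14) the text says "Clinical laboratory evaluation, routine hematology, blood chemistry, and urinalyses will be performed". The flow-sheet row agrees from visit 8 onward: "Laboratory Evaluation/Immunology | | | X | | | X | | | X", that is, visits 8, 11 and 14.

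**Injections.** The first is given at visit 8, followed by "additional 3 boosts of the TCV that will be schedule to month 1, 3, 6 (visits 9, 10, 11"). The table in section 9.4 puts the four injections on days 1, 30, 90 and 180.

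**The concern.** An endpoint needs data at the times it describes. A safety profile of ECG in a placebo-controlled trial implies at least one recording after dosing in each arm. If the visit lists are followed as written, none is made. A statistical analysis plan cannot repair this, because it cannot analyse recordings that were never scheduled.

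A numerical laboratory limit is useful mainly for changes that the patient does not feel. Such a limit can act only when a result exists. If no test is scheduled while injections are being repeated, the limit depends during that time on someone ordering a test for another reason. In a Phase I/II trial that lists safety among its primary endpoints, the schedule and the discontinuation criteria should fit together.

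**Working it through.** The protocol states no figure on this point, so there is none to reproduce. The check is a count on the visit schedule, using the flow sheet, the injection table in section 9.4, and the visit lists in sections 9.1 and 9.3 to 9.6.

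| Visit | Time | Injection | Routine laboratory tests | ECG |
|---|---|---|---|---|
| 1 | screening | none | yes (9.1; not marked in the flow sheet) | yes (9.1) |
| 8 | month 0, day 1 | 1 | yes, before randomization | not listed |
| 9 | month 1, day 30 | 2 | not listed | not listed |
| 10 | month 3, day 90 | 3 | not listed | not listed |
| 11 | month 6, day 180 | 4 | yes | not listed |
| 12 | month 8 | none | not listed | not listed |
| 13 | month 10 | none | not listed | not listed |
| 14 | month 12 | none | yes | not listed |

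**ECG.** Visits 8 to 14 are seven visits, and ECG is listed at 0 of them. The flow sheet has no ECG row. Section 7.7 does time the vital signs before and after dosing but leaves ECG in the same list untimed, so no timing can be borrowed from there. One recording per patient, made before randomization, gives no change and no treatment comparison.

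**Laboratory tests.**
- The first scheduled test after dosing is at visit 11, day 180. Time from injection 1: 180 − 1 = 179 days.
- Injections given strictly before that visit: 1, 2 and 3, so 3 of 4.
- Injection 1 cannot have a post-dose result before it, and it does have the visit 8 baseline test. The injections that could have had a scheduled post-dose result and clearly do not are injections 2 and 3, so 3 − 1 = 2.
- Injection 4 is at the same visit as the test. The protocol does not say whether blood is drawn, or the result read, before the injection. Sections 10.3 and 10.6 have the cells irradiated one day before administration. That shows when the dose is prepared, but it does not settle whether the injection waits for a result.
- The next scheduled test is at month 12: 12 − 6 = 6 months after visit 11.

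The flow sheet and sections 9.3, 9.4 and 9.6 agree on visits 8, 11 and 14, so the gap is not an artefact of a badly read table.

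**The case against.** The strongest reply is that patient safety does not rest on scheduled blood tests alone, and this stands:

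- Section 5.1 allows unscheduled visits for adverse events.
- Section 7.7 has side effects watched closely for 7 days after each injection, with physicians reachable by telephone.
- Section 9.4 follows adverse events at every visit.
- Section 9.7.2.1 opens with intolerable events of grade III or IV and names severe hypersensitivity. Neither has to wait for a scheduled laboratory test.
- Section 9.7.2.2 has clinically significant laboratory changes reported and followed.

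A reader might infer from the schedule that the safety plan as a whole cannot work, or that patients are unprotected during dosing. The documents do not support that. What remains is narrower: these safeguards are driven by symptoms or events, and none of them schedules a laboratory test between visits 8 and 11. Section 5.3 does speak of assessments every three months, but it means clinical, MRI and optional immunological assessments of the treatment effect and names no safety laboratory test.

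A reader might also infer that the limits cannot act until all four injections have been given. That is not shown, because the order at visit 11 is undefined; if the result is read first, the limits could act before injection 4. Nor are the criteria confined to the dosing period. They govern withdrawal at any time before the termination visit, so a month 6 result can still trigger them. The laboratory safety endpoint itself can be analysed, since it has values at months 0, 6 and 12.

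Finally, a reader might see a contradiction in a limit on creatinine clearance when section 7.6 measures only serum creatinine, or in the absence of a renal entry threshold. This is weak. Creatinine, weight and age are all collected, so clearance could be estimated, although no method is named. The exclusion of active systemic disease and the screening chemistry give some cover at entry.

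On ECG there is no comparable answer.

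**Conclusion.** The point holds in two parts of unequal strength.

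The ECG part holds fully. A stated secondary safety endpoint has zero scheduled post-dose recordings for all 30 planned patients and cannot be derived from the schedule as written. It would be answered only if recordings are scheduled in a document not shown here, such as a study manual; the protocol's own lists would still need to match.

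The laboratory part holds as a gap in the schedule. For about 179 days, covering injections 2 and 3, no scheduled laboratory result is available to trigger the limits in section 9.7.2.1, and the position for injection 4 is undefined. In that time a symptomless laboratory change would come to light only through unscheduled testing. This assumes that the nominal days are kept and that no unscheduled test is done. It says nothing about how likely such a change is, and it does not mean that the limits or the test times are clinically wrong.

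Both parts are worth correcting before enrolment, and neither makes the trial unworkable.

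**What to change.** - **Laboratory:** reconcile section 9.4, the flow sheet and section 9.7.2.1 so that the laboratory schedule supports the limits the protocol sets, and state the order of sampling, result and injection at visit 11.
- **ECG:** reconcile the endpoint lists (synopsis and section 4) with section 7.7, the flow sheet and the visit lists in sections 9.3 to 9.6. Either schedule the recordings that the endpoint needs or remove ECG from the secondary safety endpoints.

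The timing of tests and the limits themselves are for the sponsor's clinicians, and none is proposed here. The cost is a flow-sheet amendment with matching text, plus some routine tests at visits that already exist. If ECG is removed as an endpoint, that part costs only the change of text.
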